## ANNEX XI - Participant's pre-operative pathway and intervention delivery diagram

[figure not shown]

## ANNEX XII – Critical Care Nurse’s checklist

Table 1. Nursing Checklist Daytime

| N | Nursing Checklist Daytime (8am – 8pm)                                                               | Tick as appropriate                                                                                                                                                                                                                                                            |
|----------|-----------------------------------------------------------------------------------------------------|--------------------------------------------------------------------------------------------------------------------------------------------------------------------------------------------------------------------------------------------------------------------------------|
| 1 | Did the patient have any unknown visual/auditory impairment?                                        |  Yes  No                                                                                                                                                                                                                       |
| 2 | Were any visual/auditory aids (eg. glasses/hearing aids) in place during the intervention delivery? |  Yes  No  N/A                                                                                                                                                                                          |
| 3 | Was the family intervention delivered 3 times during the day (8am-8pm)?                             |  Yes  No
Times: 1. ____:____; 2. ____:____; 3. ____:____                                                                                                                                                                    |
| 4 | Did the patient express any verbal/non-verbal emotions when watching the video?                     |  Yes  No
If “Yes”, please specify: ____                                                                                                                                                                                     |
| 5 | Did the patient look at the digital photo frame during the day?                                     |  Yes  No
If “Yes”, how many times: ____                                                                                                                                                                                     |
| 6 | Did the intervention impact ICU nursing care?                                                       |  Yes  No
If “Yes”, please specify: ____                                                                                                                                                                                     |
| 7 | Was the family intervention delivered without any untoward events (eg., acute distress)?            |  Yes  No
If “No”, please specify: ____                                                                                                                                                                                      |
| 8 | Did the patient request to watch the video more than 3 times a day?                                 |  Yes  No
If “Yes”, please specify the total number of times: ____                                                                                                                                                           |
| 9 | Did the patient develop delirium during the day (8am-8pm)?                                          |  Yes  No
9a. If “Yes”, was the video played again?
 Yes  No
9b. If “Yes”, did it improve delirium status?
 Yes  No |

Table 2. Nursing Checklist Night-time

| N | Nursing Checklist Night-time (8pm – 8am)                          | Tick as appropriate                                                                                                                                                                                                                                                            |
|----------|-------------------------------------------------------------------|--------------------------------------------------------------------------------------------------------------------------------------------------------------------------------------------------------------------------------------------------------------------------------|
| 1 | Were any visual/auditory aids removed prior to sleep?             |  Yes  No                                                                                                                                                                                                                       |
| 2 | From a nurse’s perspective, how many hours did the patient sleep? | _____ hours                                                                                                                                                                                                                                                                    |
| 3 | Did the patient request to watch the video overnight?             |  Yes  No
If “Yes”, how many times: ____                                                                                                                                                                                     |
| 4 | Did the patient develop delirium overnight?                       |  Yes  No
4a. If “Yes”, was the video played again?
 Yes  No
4b. If “Yes”, did it improve delirium status?
 Yes  No |
| 5 | Was the iPad plugged in to charge overnight?                      |  Yes  No                                                                                                                                                                                                                       |

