This is a mixed methods research study including the collection of data from patient's medical notes, interviews and quality of life questionnaires in accordance with the schedule of assessments (SoA, Annex I). This study also involves the implementation of an auditory-visual sensory stimulation package in the cardiac ICU at ICHT to participants enrolled in the study. Digital photos will be shown continuously at the patient bedside after cardiac surgery and will always have reference to time and date. Additionally, videos will be played throughout participants' stay in ICU for at least three times per day and upon participant request. Videos will be also played when participant show signs of ICU delirium with the aim of reducing delirium incidence and improve overall better health outcomes. Simultaneously, primary outcomes measures (CAM-ICU, a routine delirium screening measure) will be collected by the research team, as this is evaluated twice a day as per usual standard of ICU practice, with the aim of assessing whether patients develop delirium during their stay in ICU.

Interviews with patients and families/friends will be held in three different occasions. The first one will be on the same day as ICU discharge, the second interview will be on the day of hospital discharge and the third one will be carried out up to a month following hospital discharge during their clinical follow-up appointment. Where possible, family members/friend and patient's interviews will be conducted together (dyadic interviewing), but the possibility of performing interviews separately will be given, so that participants feel able to discuss opinions freely without influence. Nurses' interviews will be held as a one-off and after they have provided direct care to participants who received the proposed intervention.

Each patient will be followed up daily on the wards and once at the monthly follow-up clinic up after ICU discharge, where cognitive and emotional assessments will be performed to evaluate delirium outcomes. The research team will also collect relevant information from participant's medical notes if any complications post ICU discharge arise during inpatient and follow-up stages.

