care consultants, two critical care nurses and one clinical academic research nurse (Annex XIII). Family members and friends will be requested to not deviate from the draft script order of events and to frequently mention the patient's name at the beginning/end of sentences when recording the video. They will be also asked to provide personalised messages in the second part of the video and to use simple terms equivalent to a 5th-grade reading level. The research team expects that part A) of the video to be similar between study participants, but part B) tailored to each individual participant.

Additionally, as previously agreed and supported by the critical care nursing lead for the ICU at Hammersmith Hospital, all critical care nurses will contribute to the study by filling in a daily checklist (Annex XII). This checklist will help the research team to understand the impact of the study intervention and if participants developed ICU delirium. Moreover, as per standard ICU practice at ICHT, patients following cardiac surgery will be closely monitored and primary outcomes regularly collected by critical care nurses.

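### The nurse checklist asks only whether delirium developed in the shift, so a replay given during continuing delirium is either unrecorded or logged under a new onset, depending on the nurse

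*Protocol*

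**What the plan says.** All references are to the protocol.

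**The delirium items.** Annex XII, Table 1 (daytime), item 9 asks "Did the patient develop delirium during the day (8am-8pm", answered Yes or No. Only after a Yes does the nurse reach 9a, "was the video played again", and 9b, "did it improve delirium status". Table 2 (night-time), item 4 asks "Did the patient develop delirium overnight" and nests 4a and 4b in the same way.

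**The other items on video plays.** Daytime item 3 asks "Was the family intervention delivered 3 times during the day (8am-8pm" and gives three time slots. Daytime item 8 asks "Did the patient request to watch the video more than 3 times a day". Night-time item 3 counts plays the patient asked for overnight.

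**The replay trigger.** Section 3 says: "Videos will be also played when participant show signs of ICU delirium". Section 4.6 (Patients Regaining Consent) ties the repeat of the last video to the diagnosis of delirium. Section 6.1 (Study Intervention) ties it to the patient developing delirium, subject to the personal consultee's agreement.

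**What the checklist is for.** Section 6.1: "This checklist will help the research team to understand the impact of the study intervention and if participants developed ICU delirium".

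**Delirium status elsewhere.** Section 3 has CAM-ICU assessed twice a day and collected by the research team. Section 6.1 has it extracted from the medical record, and Annex I schedules it on D0 to D3.

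**The concern.** The two delirium items ask about onset within one 12-hour shift. No item asks whether delirium was present, continuing or resolved. A nurse who takes over a patient who is already delirious has no answer that fits. A literal No closes the replay and response questions. A loose Yes opens them, but states that delirium developed again.

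The primary objective (Section 2.1) is feasibility and acceptability. Whether staff can deliver a replay to a delirious patient, and what follows, is part of that. The checklist is the only structured record of this that the protocol describes. With 12 patients, and only some of them delirious, inconsistent completion in a few longer episodes could noticeably change what the study can report. Information not written down during the shift may not be recoverable later.

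**Working it through.** The plan gives no figure to reproduce. The check is a reading of the form's skip logic, followed by simple counting.

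**Step 1. Can a delirium-triggered replay be recorded anywhere else?**

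- Daytime item 3 covers the three scheduled plays only.
- Daytime item 8 covers plays the patient requested beyond three.
- Night-time item 3 covers plays the patient requested.
- Items 9a and 4a cover a replay for delirium, but only after a Yes to 9 or 4.

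So a replay that staff start because of delirium has no place outside 9a and 4a. A replay that the patient happened to request could still appear under item 8 or night-time item 3.

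**Step 2. What does one episode produce?** Let an episode span k consecutive shifts, with k assumed because the protocol gives no duration.

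- Literal reading: Yes answers = 1; shifts with the replay items closed = k - 1; share closed = (k - 1)/k.
- Loose reading: Yes answers = k, so one episode is recorded as k onsets.

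Annex I places the ICU intervention on D1 to D3, which gives at most 3 × 2 = 6 shift forms on that schedule. Taking onset in the D1 day shift, k runs from 1 to 6:

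| k | Literal: Yes answers | Literal: shifts with replay items closed | Share closed | Loose: onsets recorded |
|---|---|---|---|---|
| 1 | 1 | 0 | 0/1 = 0% | 1 |
| 2 | 1 | 1 | 1/2 = 50% | 2 |
| 4 | 1 | 3 | 3/4 = 75% | 4 |
| 6 | 1 | 5 | 5/6 = 83% | 6 |

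The closed shifts are those in which a replay, if given, cannot be recorded. They are not a count of replays lost. Whether a patient was ever delirious comes out correctly under both readings, provided the onset shift is ticked.

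**Step 3. Are replays after the onset shift foreseen?** The Section 3 trigger is signs of delirium and is not limited to onset, so replays in later shifts are possible under it. Sections 4.6 and 6.1 refer to diagnosis and development. Under those, fewer replays would fall outside the onset shift. The form's wording matches Section 6.1 and fits Section 3 poorly.

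**The case against.** The case on the other side has several sound parts.

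- **Onset wording has a use.** Section 2.2 seeks the incidence of newly diagnosed delirium, and Section 6.1 says the checklist should show whether delirium developed. This stands. The fault is the missing category for continuing delirium and the nesting beneath the onset question.
- **CAM-ICU preserves delirium status.** This also stands. A reader might infer that the study will miss delirious patients or misstate incidence, but the documents do not support that. CAM-ICU does not, however, show whether a replay was given or what followed.
- **Two of the three trigger statements point to onset or diagnosis.** A reader might infer that every delirious shift calls for a replay, so that every closed shift is a lost replay. Sections 4.6 and 6.1 do not say so, and Section 3 does not state it outright. This limits the size of the loss but leaves the form at odds with Section 3.
- **No episode count or replay-delivery rate is a named outcome.** Sections 3.1 and 7 list neither, so repeated onsets corrupt no stated endpoint. The principal investigator also delivers the intervention alongside the nurses, and the nurse interviews cover acceptability and usability. These give some view of delivery, but not a shift-by-shift record.
- **Any single percentage depends on the durations chosen.** Assumed episodes of 1, 4 and 2 shifts would give 3 Yes answers for 1 + 4 + 2 = 7 delirious shifts on the literal reading (4/7 = 57% closed). On the loose reading they would give 7 onsets for 3 episodes (7/3 = 2.3-fold). Such figures illustrate the mechanism and estimate nothing.
- **Nurses will not uniformly answer No.** Agreed. Inconsistent completion is the likelier result, and that is the concern here.

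**Conclusion.** The point holds as a defect in data capture. Items 9 and 4 cannot record continuing delirium as such, and they are the only route to the replay and response questions. A replay given in a later shift of the same episode is therefore either unrecorded or entered under a new onset, depending on how the nurse reads the item.

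Its size cannot be fixed from the protocol. It is zero if every episode stays within one shift, and up to k - 1 of k shifts for an episode spanning k shifts. It also depends on which replay trigger applies, since the loss is real only where replays are given after the onset shift. Delirium incidence and the ever-delirious status of a patient are not threatened, given CAM-ICU and a ticked onset shift. What is affected is the feasibility record of delirium-triggered replays and the checklist's stated purpose of showing the intervention's impact. That justifies a correction, though the consequence is modest.

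**What to change.** 1. Reword daytime item 9 and night-time item 4 to: *Was the patient delirious at any time in this shift? No / Yes, new in this shift / Yes, continuing from an earlier shift.*
2. Open 9a/9b and 4a/4b for either Yes.
3. Count new delirium from the *new* answers only, so that the onset information is kept.
4. Separately, reconcile the replay trigger across Sections 3, 4.6 and 6.1, and with the form. Which trigger applies is for the study team. Any denominator for replay delivery should follow the trigger they confirm. Using all delirious shifts would presume a rule that the documents leave in conflict.

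The cost is a wording change to two items and one extra tick box on each, made as a small amendment to Annex XII. Nurses would need to know the previous shift's delirium status, which handover and the twice-daily CAM-ICU record should supply. The form change affects only what is recorded and not what care is given.

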## **ANNEX XIII - Video Guided Script Template for Family Members/Friends**

### VIDEO GUIDED SCRIPT TEMPLATE FOR FAMILY MEMBERS/FRIENDS

This draft script of reorientation and reassurance messages was initially developed based on published research and considering patients' memories from their lived ICU experience(s). Subsequently, it was further refined through coproduction within a lay focus group of patient and public members (with ICU lived experience) and reviewed by an expert panel comprising two critical care consultants, two critical care nurses and one clinical academic research nurse.

The template below highlights what will need to be covered during the 3-minute videos and in which order of events this would be ideal to be recorded by participants. This script will assist family members/friends to follow a clear and structured speech, as well as, allow them to better prepare for the video recording process.

Family members and friends will be requested to not deviate from the draft script order of events and to frequently mention the patient's name at the beginning/end of sentences when recording the video. They will be also asked to provide personalised messages in the second part of the video and to use simple terms equivalent to a 5th-grade reading level.

By following this script, the research team expects that part A) of the video to be similar between study participants, but part B) tailored to each individual participant. Videos will be divided into two main parts:

#### **A) Reorientation**

- Start the video by greeting the patient and mentioning their name.
- Introduce yourself (e.g., name/preferred name) and your relationship to the patient.
- State where you are (e.g., house, garden, etc.) and if you are alone or accompanied (e.g., with significant others, pets, special objects/toys)
- Mention the patient's name in the beginning/end of the next sentences
- Provide a reference to the approximate time (9am, 2pm or 6pm) and date (e.g., Wednesday)
- Mention that patients have now had their surgery and are staying in Intensive Care at Hammersmith Hospital in London.
- State how many days have been since surgery (e.g., today is day 1 after your cardiac surgery)

#### **B) Reassurance**

- Continue the video by explaining that this is a recorded video/message to help patients understand what is going on around them.
- Family members should then choose from the following options but are also free to personalise the next one or two final sentences of the video.

Examples of reassurance and supportive messages:

- 1) It is OK, do not be scared.

- 2) You will soon be home with us.
- 3) Your nurses and doctors are here looking after you and helping you recover.
- 4) You might be uncomfortable or in pain, but the nurses are making you more comfortable and giving you painkillers.
- 5) It is loud and noisy because of the machines that are helping you get better.
- 6) You may have some wires and tubes in place to help you recover.
- 7) You may have something on your wrists to keep you from pulling at the wires and tubes by accident, but this will soon be removed.
- 8) You can't talk right now because of your breathing tube, but the nurses know you might be uncomfortable and are giving you medicine for that.

- Finish the video with a farewell message (e.g., see you soon) and mention the patient's name at the beginning/end of the sentence.

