## **3. STUDY DESIGN**

The study will be conducted over twelve months in the Cardiac Intensive Care Unit at Hammersmith Hospital, Imperial College Healthcare NHS Trust. For this study, a total of 30 individuals (12 patients, 12 family members or close friends and 6 critical care nurses) will be recruited and interviewed to allow sufficient depth and richness of data. Patients and family members/friends will be mainly recruited from the ICHT pre-operative clinic outpatient department, which runs several pre-operative clinics per week. Each week, approximately eight patients undergo cardiac surgery, and the research team intends to recruit one patient and their family member/friend per a week for a period of 4 months.

All participants will be given time to consider their participation in the study and if happy will be consented by PI or other delegated member of the research team. Patients will be approached during one of their pre-operative clinic appointments and informed consent will be sought at this stage. Once written consent has been obtained, patients will be asked to nominate a family member or friend to be contacted by the PI. After signing the consent form, family members/friends will also be enrolled into the study and requested to self-record short videos pre-operatively (based on a guided script - ANNEX XIII), which will be safely uploaded to an iPad. In addition, patients will be requested to select multiple pictures, which will be securely uploaded into a digital photo frame. This package combination of videos and pictures will be shown to patients post-operatively in ICU. Critical care nurses will be recruited after they have provided direct care to at least one participant, who received the study intervention in ICU.

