### Patients Regaining Consent

Patients undergoing cardiac surgery require mechanical ventilation and sedation to remain in an induced coma throughout the theatre procedure and for a short period of time after being admitted to ICU. Thus, patients' mental capacity is expected to fluctuate during the research study and patients will be unable to promptly re-consent to the study upon ICU admission.

The intra-operative stage is not included in the design for this research study; hence no direct study interventions will be performed on patients during this period. However, the research team may collect any relevant intra-operative information specified in the participant's electronic medical notes, which will happen retrospectively to the operation and written consent for data collection will be sought from participants prior to the procedure.

When appropriate, the study team will re-consent participants in ICU once they are clinically stable, fully awoken from the anaesthesia and have regained the capacity to remember and understand the details of the study. A member of the research team obtaining re-consent will offer to explain the study again and allow time for patients to reconsider their participation in the study. The study will then resume as planned in ICU when participants sign a Patient Regaining Capacity Consent Form (Annex VIII) and express that are happy to proceed with the study intervention in ICU. After written consent is obtained, a copy will be uploaded to medical records (e.g., Cerner), another copy will be given to the patient, and the original

document will be retained in the ISF, which will be stored in a key-locked cabinet inside the CI's office.

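### Annex XIII example 8 tells the patient as fact that a breathing tube prevents speech; it is recorded before surgery, not tied to the patient's state when played, and likely untrue on the main section 4.6 route

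*Protocol*

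**What the plan says.** Section 3 of the protocol states that family members or friends are "requested to self-record short videos pre-operatively", following the guided script in Annex XIII. Part A of the script gives each clip an approximate clock time and a count of days since surgery. Part B lists eight example messages, and "Family members should then choose from the following options but are also free to personalise" the closing sentences.

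Example 8 in that list tells the patient that they cannot "talk right now because of your breathing tube, but the nurses know you might be uncomfortable". Example 6 is worded differently: "You may have some wires and tubes in place to help you recover". Examples 4 and 7 also open with a might or a may.

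Section 4.6, under Patients Regaining Consent, expects ventilation and sedation in theatre and "for a short period of time after being admitted to ICU". Re-consent is sought from patients "once they are clinically stable, fully awoken from the anaesthesia and have regained the capacity to remember and understand the details of the study". It then says: "The study will then resume as planned in ICU when participants sign a Patient Regaining Capacity Consent Form". The same section also lets participation resume with a personal consultee's involvement when the patient cannot consent, and after an urgent deterioration that requires ventilation. Section 8.2 asks for the form where possible, and ideally before the study resumes.

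Annex I marks the intervention on D1 to D3. Section 6.1 sets three scheduled plays a day, using different videos, and has the last video shown played again when delirium develops, subject to the consultee's agreement. Section 4.6 has the same replay on a delirium diagnosis.

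**The concern.** The intervention is meant to reorient and reassure. Example 8 makes a specific claim about the patient's body that the patient can check at once. It is fixed before surgery by someone who cannot know whether it will hold. A patient who is awake and has just signed a form would in most cases hear a relative describe a situation that is not theirs.

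Two things are at stake. One is the fidelity of the intervention's content to its own aim: a reorientation video should not contain a statement that is wrong about the patient's present condition. The other is interpretation of the primary objective, feasibility and acceptability. Reactions to a script fault that could have been removed beforehand would be mixed with reactions to the intervention itself. The replay rule adds to the concern, because it selects the most recent clip whatever its content.

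**Working it through.** The protocol states no figure on this point, so the check is mainly a comparison of sections, with one hand count to see what can be said about frequency.

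**Step 1: is the message conditional?** Examples 4, 6 and 7 concern discomfort, wires and tubes, and wrist restraints, and each opens conditionally. Example 8 concerns a breathing tube and loss of speech, and is stated flatly.

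**Step 2: can the family know whether it applies?** No. Recording is pre-operative. Part A adapts each clip to things known in advance (clock time, days since surgery). Whether a tube is in place at a given play is not known in advance.

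**Step 3: who sees the videos under section 4.6?**

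| Route | Patient state described | Fit with example 8 |
|---|---|---|
| Re-consent in ICU | Stable, fully awake, capacity regained, form signed | Unlikely to fit |
| Cannot consent, consultee approached (delirium is the example given) | Lacks capacity; a tube is neither stated nor excluded | May or may not fit |
| Urgent deterioration, pre-operative consent plus consultee agreement | Induced coma for ventilation is the example given | Could fit |

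The first row is an inference. Section 4.6 does not mention tube removal, but a short period of ventilation, full waking and a signed form together make the message improbable.

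**Step 4: does any text match the clip to the patient?** None that is visible. The nurse checklist in Annex XII records delivery times, emotions, untoward events and replays, but not whether the content applied. The Annex XI diagram, to which section 6.1 refers for delivery, is not shown and cannot be checked.

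**Step 5: how often would the line be untrue?** Scheduled plays on the Annex I days: 3 per day × 3 days = 9. Assume, for illustration only, that all 9 take place and that every clip contains example 8. The untrue plays are those after tube removal:

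| Tube removed | Untrue plays |
|---|---|
| Before 9am on D1 | 9/9 |
| Between 9am and 2pm on D1 | 8/9 |
| Between 7pm on D1 and 9am on D2 | 6/9 |
| Between 9am and 2pm on D2 | 5/9 |
| Between 2pm and 7pm on D2 | 4/9 |
| Still in place through D3 | 0/9 |

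The crossover to a majority is therefore removal before the 2pm play on D2. If only some clips carry the line, the share falls in proportion; if no family chooses it, it is 0. The protocol fixes neither the removal time nor the uptake, so the whole range from 0/9 to 9/9 remains open.

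**Step 6: after rewording.** A conditional sentence is not untrue on any route in Step 3 or any row in Step 5, whatever the removal time.

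**The case against.** The strongest counter-argument is that a breathing-tube message has a legitimate place in the list. The consultee routes in section 4.6 allow videos to be played to patients without prior re-consent, and ventilation is named there. This stands. A reader might infer that the videos start only in fully awake patients able to re-consent, so that Annex XIII flatly contradicts section 4.6. The documents do not support that, and section 8.2 softens the form requirement further. What remains is that nothing visible confines the line to patients for whom it is true.

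The line is also optional: it is one of eight examples, and part B is meant to be personal. This stands too, and it limits how often the problem can arise. A reader might infer that the line is untrue at most plays, or try to count the patients exposed. Neither can be derived, for the reasons in Step 5.

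Other examples are unconditional as well, such as the promise of being home soon and the remark about noise, and the script was reviewed by lay members with ICU experience and an expert panel. Both are fair. But the remark about noise concerns the surroundings and the promise of home the future, whereas example 8 asserts a present bodily state. The review does not reconcile the line with section 4.6.

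Finally, a feasibility study exists partly to find script problems, and no text in the protocol shows that the line would cause harm. That is correct: added confusion is a plausible concern, not a documented effect. It is still better to remove a fault that can be seen beforehand.

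**Conclusion.** The point holds as a minor but real inconsistency in the content of the intervention. Example 8 is optional, unconditional, fixed before surgery and, in the visible text, unconnected to the patient's state when played. It is likely untrue for patients on the main re-consent route and could be true for some who continue through a consultee. The last-video rule could repeat it to a patient with delirium to whom it does not apply.

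Its frequency is undetermined. The conclusion rests on one inference, that a fully awake patient who has signed the form is unlikely to have a breathing tube in place, and on the missing Annex XI diagram containing no matching step. Sample size, endpoints and analysis are not affected.

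**What to change.** Reconcile example 8 in Annex XIII with the resumption routes in section 4.6 and the replay rule in sections 4.6 and 6.1. The simplest way is to reword example 8 conditionally, in the manner of examples 4, 6 and 7, so that it is not untrue whichever route the patient is on. This changes script wording only; it adds no bedside rule and takes no position on when, or to whom, videos should be played.

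The cost is one line of text and a minor amendment, since the script is participant-facing. Any family that has already recorded example 8 as it stands would need to be identified, so the change is best made before recordings begin.
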